### 3.7 Data collection

The collection of venous access data will be prospective and will occur through *on-site visits*, based on the electronic medical record, records in the medical record and direct visualization of care routines related to vascular access practices.

All observations will be entered into a portable electronic device and included by the researchers in an electronic data capture tool, developed via *Research Electronic Data Capture (REDCap)* software.

The processes involving the insertion and follow-up of catheters in the first 24 hours and daily until catheter removal, death or 30 days (whichever occurs first) *will be evaluated in loco*.

The costs related to the use of the two catheters will be evaluated through micro-costing, with an analysis of individual care costs, and the data will be obtained from the purchasing sector and technical opinion of the institution.

### 3.9 Data Collection Forms

Participant data will be collected through the application of the following forms: Baseline and Insertion Data (APPENDIX B), Daily Monitoring (APPENDIX C), Insertion Failure (APPENDIX D), and Excluded Patients (APPENDIX E).

**a. Baseline and Insertion Data:** sociodemographic and clinical data - including application of the Charlson Comorbidity Index, *the* assessment of difficult venous access and those referring to the patient's current hospitalization and information related to the ultrasound-guided peripheral venipuncture procedure.

**b. Daily Monitoring:** data regarding the follow-up of the inserted catheter (characteristics and possible complications). Applied daily by the team's researchers.

**c. Insertion Failure:** form where all patients in which insertion failure occurs, regardless of group, will be registered.

**d. Excluded Patients:** record of the patients who were excluded from the study, the reason and the stage of exclusion, completed by the team researchers.

Figure 01 shows the summarized flowchart of the study protocol.

[figure not shown]

**Figure 01. Summary flowchart of the study protocol**

### **3.10 Data analysis**

The data will be entered into the REDCap database and extracted for analysis in the *Statistical Package for the Social Sciences - SPSS v.21*. Continuous variables will be described as mean and standard deviation for those with normal or median distribution and interquartile range for asymmetric variables. The *Kolmogorov-Smirnov and Shapiro Wilk* tests will be used to test the normality between the quantitative variables. Categorical variables will be expressed as percentages and relative frequencies. Quantitative variables will be compared using Student's t-test or Mann-Whitney test according to data distribution. The associations of the clinical characteristics of the patients will be performed using Pearson's chi-square test. The groups will be compared in relation to complication-free survival by *Cox analysis* and *long-rank* test. A  $P < 0.05$  will be considered statistically significant.

The analysis regarding microcosting will occur through a decision tree model in which hospitalized adult patients can be allocated to the use of a *Midline catheter* or a long peripheral venous catheter.

These patients will be subject to the occurrence of composite outcomes such as infiltration, phlebitis, occlusion, accidental removal, catheter-associated bloodstream infection, and deep vein thrombosis. The economic outcomes will be the costs of using the *Midline Catheter and the Long Peripheral Intravenous Catheter* and the resolutions of infiltrations/extravasation, phlebitis, occlusions, catheter-associated bloodstream infection, and deep vein thrombosis. The values will be expressed in reais and the analysis will be performed between the absolute and percentage difference between the number of composite outcomes and cost between the two groups studied (*Midline catheter* and long peripheral intravenous catheter).

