### **2.2 Specific objectives**

- Analyze the indicators of good practice:

- a) Time of permanence of the venous access device free of complications: (infiltration, phlebitis, occlusion, accidental removal, catheter-associated bloodstream infection and deep vein thrombosis);
  - b) Rates of bloodstream infections associated with the type of catheter used;
  - c) Occurrence of deep vein thrombosis associated with the type of catheter;
  - d) Success rate in the first puncture attempt related to the type of catheter;
- Perform the economic analysis of the incorporation of the technology – midline catheter:
- a) Comparison of the cost of the two technologies used, type of catheter;
  - b) Costs of treatment of isolated or combined complications and catheter replacements resulting from associated infections;
  - c) Cost of avoided complications;

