### **3. METHOD**

#### **3.1 Design**

This is a randomized, parallel, open-label, controlled, single-center clinical trial, blinded to statistical analyses. In clinical trials, the investigator applies an intervention and observes its effects on outcomes. The main advantage of a clinical trial over an observational study is its ability to demonstrate causality. This study will be registered on the Platform *Clinical Trials* and will strictly follow the guidelines of the *Consolidated Standards of Reporting Trials* (CONSORT).

The economic evaluation will be based on micro-costing where all cost components are defined at the most detailed level from individual patient treatment data, such as from the medical record review. The unit of analysis in micro-costing is the individual service.

Considering the perspective of the public health system, the method seeks to assess costs as accurately as possible, including the direct and indirect costs of patient care. The time horizon considered will be 30 days. Bottom-up micro-costing will be carried out, as this is considered the gold standard for economic evaluations in health, considering that the collection of individual data enables a higher level of precision in the estimation of costs.

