### **3.11 Bioethical considerations**

This study will be developed in accordance with the Guidelines and Regulatory Standards for Research involving human beings, approved by the National Health Council, Resolution No. 466/12 of the National Health Council.

The informed consent form will be used for all patients or their legal guardians. Participants will only be included in the study after understanding and agreeing to participate in the study by signing the Informed Consent Form (ICF) (APPENDIX A).

The project will be submitted to the Research Committee of the School of Nursing, Federal University of Rio Grande do Sul and to the Research Ethics Committee of the Hospital de Clínicas de Porto Alegre.

The researchers declare that they maintain the term of commitment for the use of data and confidentiality of all information collected at the institution.

**Risks:** regarding the risks, the present study does not confer additional risk, considering those related to the peripheral venipuncture procedure, which are characterized by insertion failure, arterial puncture, hematoma, infiltration, extravasation, occlusion, bacteremia, cellulitis, catheter-associated bloodstream infections, phlebitis, accidental removal of the device, and thrombosis.

**Benefits:** according to the results expected by the study, if the *midline catheter* demonstrates superiority to the long peripheral venous catheter, demonstrating longer time of use without complications and cost effectiveness, this technology can be incorporated into the institution's care routine and also into the public health system, increasing safety and improving the quality of care for hospitalized clinical adult patients.

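### Section 3.10 costs five of the six tree events, gives insertion failure no branch or cost, and words the economic comparison without a denominator

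*Protocol*

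**What the plan says.** Section 3.10 subjects patients in the decision tree to "composite outcomes such as infiltration, phlebitis, occlusion, accidental removal, catheter-associated bloodstream infection, and deep vein thrombosis". The next sentence gives the economic outcomes: the costs of using each of the two catheters, "and the resolutions of infiltrations/extravasation, phlebitis, occlusions, catheter-associated bloodstream infection, and deep vein thrombosis". The comparison is then described: "the analysis will be performed between the absolute and percentage difference between the number of composite outcomes and cost between the two groups studied".

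Section 2.2 lists three economic objectives. Item (a) compares the cost of the two technologies. Item (b) is "Costs of treatment of isolated or combined complications and catheter replacements resulting from associated infections". Item (c) is "Cost of avoided complications".

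Section 3.1 sets a wide scope. In the micro-costing, "all cost components are defined at the most detailed level from individual patient treatment data", from the public health system perspective, "including the direct and indirect costs of patient care", with a 30-day horizon. In section 3.8, follow-up runs to the earliest of catheter removal or replacement, discharge, death, or 30 days. The same section uses simple randomisation and says that after a failed puncture the care team may move to oral treatment, hypodermoclysis, a PICC or another central catheter.

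Section 3.11 gives the intended use: incorporation if the midline shows superiority, "demonstrating longer time of use without complications and cost effectiveness".

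**The concern.** Three statements of what is costed (2.2(b), 3.1 and 3.10) do not agree. An analyst who follows the itemised lists would count an accidental removal as an effect and enter no cost for it. A failed insertion would drop out of the model altogether, although the access that follows is a consequence of how the allocated device performed.

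The comparison is worded in numbers of outcomes and in cost, without saying per what. Simple randomisation rarely gives equal arms, so a difference in totals would mix the device effect with the difference in arm size. Section 3.10 also does not say how cost and effect are to be combined, although 2.2(c) implies that they will be and 3.11 relies on cost effectiveness.

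At stake is the economic result on which the incorporation proposal partly rests. The primary clinical outcome is not affected.

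**Working it through.** **Step 1. Tree events against costed events (3.10), with the replacement cost named in 2.2(b).**

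| Event | In tree | Resolution costed | Replacement named in 2.2(b) |
|---|---|---|---|
| Accidental removal | yes | no | no |
| Infiltration | yes | yes | no |
| Phlebitis | yes | yes | no |
| Occlusion | yes | yes | no |
| Bloodstream infection | yes | yes | yes |
| Deep vein thrombosis | yes | yes | no |
| Insertion failure | no | no | no |

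Six events are in the tree and five have a costed resolution. Section 3.6.2 defines accidental removal as early removal not caused by a complication. There is then no complication to treat, and its natural cost is the new access, which no item names. The hypothesis in section 1 counts it among the events leading to removal or replacement.

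**Step 2. Horizon against follow-up.** Costs run to 30 days (3.1). Follow-up may stop at removal or replacement (3.8). The form headed Appendix D records whether the original catheter is still in place and, if not, the reason and date. It has no field for the device that replaced it. The form headed Appendix E records subsequent access, but only after a failed insertion.

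**Step 3. Effect of an omitted item on the cost difference.** Let q be the probability of the uncosted event per randomised patient and c the mean cost of the access that follows. The part left out of the mean cost difference is

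q(midline) × c(midline) − q(long) × c(long).

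This is zero if rates and follow-on costs are equal in the two arms; otherwise its sign depends on which arm is worse. The protocol gives no c and no rate of accidental removal or insertion failure, so it cannot be evaluated. As an assumed range only: if 5% to 30% of patients had an accidental removal, then 51 × 0.05 = 2.55 to 51 × 0.30 = 15.3, or about 3 to 15 patients per arm, would have no resolution cost listed.

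**Step 4. Denominator.** The planned size reproduces. With a difference of 5 days, SD 7, 90% power and 5% significance (taken as two-sided), n per arm = 2 × (1.960 + 1.282)² × 7² / 5² = 41.2, rounded up to 42, giving 84. Adding 20%: 42 × 1.2 = 50.4, rounded up to 51, giving 102.

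Under simple randomisation the size of one arm is Binomial(102, 0.5):

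- P(exactly 51/51) = 0.079
- P(arms differ by 10 or more) = 0.373
- P(arms differ by 14 or more) = 0.198

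At equal true risk, expected counts are proportional to arm size. A 46/56 split gives 56/46 − 1 = 22% more events in the larger arm; a 44/58 split gives 58/44 − 1 = 32% more. Total cost scales in the same way at equal mean cost. Per-patient figures remove this effect.

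**The case against.** The best defence is that this is loose wording, not an exclusion. The resolution of phlebitis, infiltration or occlusion can include a new catheter, the cost of using a catheter can be read to cover a second one of the same type, and 3.1 promises every component. That stands against any claim that all replacements not due to infection are left out: the texts are inconsistent, not exclusionary. It does not rescue accidental removal, which is absent from the resolution list, or insertion failure, which is absent from the model.

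A decision tree normally works with branch probabilities and expected cost per patient, and 3.10 describes categorical variables as percentages. A denominator may therefore be intended. That also stands in part: the imbalance figures matter only if totals are compared. But the sentence that defines the comparison speaks of numbers, and a few words would settle it.

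A reader might infer that cost and effect are never combined. The documents do not support that, since 2.2(c) is an objective of that kind. The fair complaint is that 3.10 does not say what it means. Interval methods and branch layout may properly sit in an analysis plan.

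Finally, the economic analysis is a secondary outcome. That limits the weight of the point without removing it.

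**Conclusion.** The point holds as an inconsistency to be reconciled. Accidental removal is counted as an effect without a listed cost, insertion failure has neither branch nor cost, replacement cost is named only for infection, cost follow-up may stop before the 30-day horizon, and the comparison has no stated denominator. The cost difference as written could leave out costs caused by device failure.

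The only size that can be given concerns the denominator: about a 37% chance that the arms differ by 10 or more, which would shift a comparison of totals by 22% or more at equal risk. This assumes 102 patients randomised 1:1 without restriction, and that totals are what is compared. The size and direction of the omitted cost cannot be computed.

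A reader might go further and infer that the model omits the main costs, for instance by setting the midline infection rate in the Introduction against the higher rates of occlusion, phlebitis and infiltration. The documents do not support this. Those rates come from two different sources, not every such event need lead to a replacement (3.6.2 allows for thrombolysis in an occluded catheter), no matching rates are given for the long catheter, and event counts are not costs. Nor does it follow that cost effectiveness cannot be assessed: costs are to be collected per patient, so a valid result is available once the quantities are defined.

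**What to change.** - In 2.2(b) and 3.10, cost all six events, every replacement access whatever the cause, and insertion failure with the access actually used. Give insertion failure its own branch.
- Capture these costs to day 30 for every randomised patient, including after removal or replacement of the study catheter. Use the medical-record review already foreseen in 3.1, or add one field for the replacement device to Appendix D.
- In 3.10, state that the comparison is of mean cost and proportion with a complication, each per randomised patient.
- Define 2.2(c) as incremental cost per complication avoided: (mean cost, midline − mean cost, long catheter) / (proportion with a complication, long catheter − proportion, midline). The method for its uncertainty can go in the analysis plan.

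The cost is a few sentences in 2.2 and 3.10, slightly more cost extraction and analysis, and possibly one form field. Sample size, allocation and the primary analysis do not change.

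### Section 3.10 fixes the cost comparison as a point difference from a decision tree with no stated uncertainty, although one costly event may decide its sign

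*Protocol*

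**What the plan says.** Section 3.1 chooses bottom-up micro-costing over a 30-day horizon because "the collection of individual data enables a higher level of precision in the estimation of costs". Section 3.10 then says: "The analysis regarding microcosting will occur through a decision tree model". The tree's outcomes are the six complications, and its costs are the two catheters plus the resolution of the complications, ending with "catheter-associated bloodstream infection, and deep vein thrombosis. The values will be expressed in reais". The comparison itself is stated as follows: "the analysis will be performed between the absolute and percentage difference between the number of composite outcomes and cost between the two groups studied".

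The preceding paragraph of 3.10 gives the clinical comparisons named tests and a 5% significance threshold. The economic paragraph has no counterpart.

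The use of the result is stated in three places:
- Section 2.2 lists what it costs to avert complications as an objective.
- The Summary proposes adoption in the public system on the basis of the results.
- Section 3.11 ties adoption to the midline "demonstrating longer time of use without complications and cost effectiveness".

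**The concern.** An absolute and a percentage difference are two ways of writing one point estimate. Neither tells a payer whether the sign is established. That matters more for costs than for most endpoints, because a few expensive events can carry much of the mean and a trial of this size will see very few of them. The sample size was set on complication-free days, not on cost. If 3.10 is followed as written, the trial could report that the midline saves or costs money when one infection more or less would have reversed the statement. An adoption argument would then rest on it.

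**Working it through.** **Sample size in play (section 3.4).** Difference 5 days, SD 7, power 90%, alpha 5% (two-sided assumed):

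n per arm = 2 × (1.960 + 1.282)² × (7/5)² = 2 × 10.507 × 1.96 = 41.2, so 42 per arm and 84 in total, as stated. Then 42 × 1.2 = 50.4, so 51 per arm and 102 in total, as stated.

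The protocol gives no figure for the precision of the cost difference, so there is none to reproduce.

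**Expected costly events in the midline arm.** The rates are those cited in the Introduction for midline catheters. They are background literature, not this trial's population.

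| Event | Rate p | 51p | Chance of none, (1−p)^51 |
|---|---|---|---|
| Bloodstream infection | 0.4% | 0.20 | 81.5% |
| Venous thrombosis | 4.1% | 2.09 | 11.8% |

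With 42 per arm the figures are 0.17 (84.5%) and 1.72 (17.2%).

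**Leverage of one event.** An event of cost C adds C/51 to its arm's mean. Let G be the extra price of a midline. If the arms are otherwise equal, one extra event in the control arm turns the difference from +G to G − C/51, which is negative once C > 51G. No unit cost appears in the protocol, so this threshold is as far as the document's own figures go.

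**What the tree does with this.** A tree multiplies event probabilities by costs, so it returns a mean and counts every observed event in full. The protocol names no outside source for the probabilities. If they come from the trial arms, an arm with no infection gets a zero-probability infection branch. Yet 0 of 51 is compatible with a risk of up to 1 − 0.025^(1/51) = 7.0% (exact 95% upper limit). A single run of the tree shows nothing of that range.

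**Illustration only.** Assumed inputs, in units of one control-catheter price: device cost 3 (midline) and 1 (control), each with 20% lognormal variation; one type of costly complication with risk 4.5% (midline) and 10% (control); 51 per arm; 3,000 simulated trials.

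- True difference (midline − control) = 2 × exp(0.02) − 0.055C = 2.04 − 0.055C.
- SD of the difference in means ≈ C × √[(0.045 × 0.955 + 0.10 × 0.90)/51] = 0.0511C.

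| C | True difference | SD by formula (simulated) | Simulated 95% sampling range | Point estimate has wrong sign |
|---|---|---|---|---|
| 20 | +0.94 | 1.02 (1.03) | −1.1 to 2.9 | 16% |
| 50 | −0.71 | 2.55 (2.55) | −5.8 to 4.1 | 43% |
| 100 | −3.46 | 5.11 (5.13) | −13.7 to 6.0 | 28% |
| 200 | −8.96 | 10.22 (10.41) | −29.4 to 10.0 | 20% |

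Every range includes zero. A second simulation took other assumptions: infection cost 50 to 200 units, infection risk 0.4% against 1–2%, thrombosis 4% in both arms at 30 units, and minor complications 15% against 30% at 2 units. It gave the wrong sign in 16% to 46% of trials. The two agree in direction, but neither estimates this trial.

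**The case against.** The strongest reply is that this is an omission. Only the protocol is at hand, and intervals, resampling and sensitivity analysis are often left to an analysis plan. The sentence also applies the same absolute and percentage difference to the number of complications, while 3.10 separately tests complication-free survival by Cox and log-rank. It may therefore name the reported measure, not the whole analysis. This stands in part: one may say that the protocol states no uncertainty, not that none will ever be reported. But 3.10 does define the economic comparison, in a section that sets tests and a threshold for its other comparisons, and it defines it as a bare difference.

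It is also fair to say that every unit cost and control risk in the illustration is assumed, and that the sentence in 3.11 is a conditional statement of benefits, not a decision rule. Both points stand. The C/51 leverage and the event counts do not depend on the assumed costs.

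A reader might go further. 3.10 describes skewed variables by median and "interquartile range for asymmetric variables" and says "Quantitative variables will be compared using Student's t-test or Mann-Whitney test according to data distribution". It is tempting to infer that costs will be compared by ranks, so that the rare expensive complications drop out. The document does not support that. The rule stands in the clinical paragraph, nothing applies it to costs, and the economic paragraph has its own method, a tree, which yields means. The two complaints also exclude each other: a rank test would bring a P value, and a tree difference involves no median.

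**Conclusion.** The point holds in a limited form. Section 3.10 fixes the economic comparison as a point difference with no stated measure of uncertainty, although the patient-level data for one are to be collected and an adoption argument is to rest on it. With about 0.2 infections and 2.1 thromboses expected in the midline arm, the sign of the difference may depend on one event. This rests on the cited background rates applying roughly to this population and on 51 patients per arm. How often the sign would be wrong cannot be derived from the document. The median and Mann-Whitney rule is not a separate error: 3.10 neither applies it to costs nor excludes them, so a clarifying sentence is enough. The primary outcome is unaffected. The change should be made because it replaces a stated method with a better one at almost no cost.

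**What to change.** In section 3.10, replace the sentence on the economic comparison with the following:

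- Mean cost per randomised patient in each arm, and the difference in means with a 95% bootstrap interval, resampling patients within arm and keeping each patient's cost and complication status together.
- Sensitivity analysis of the tree's event probabilities and unit costs. This is needed as well as the bootstrap, because resampling an arm with no infections always returns no infections.
- Incremental cost per complication avoided, with its uncertainty. This serves an objective already listed in 2.2.
- One sentence saying that costs are compared on arithmetic means and not under the section's general rule for skewed variables.

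In the Summary and section 3.11, make any cost-effectiveness statement depend on that interval.

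The cost is a few lines of code on data already planned, plus the wording changes. No extra patients or measurements are needed. The downside is that the cost conclusion will be stated less firmly, and may be that the sign of the difference is not established.
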